### Aims, hypotheses, and study design

The present study is a randomized clinical trial aimed at generating evidence in support of the effectiveness of an online group psychological counseling intervention in university students with high levels of academic burnout. To this aim, the study design entails the comparison between students that will be randomly assigned to two matched groups: (1) a psychological counseling group (PC, *N* = 65) or (2) a waiting list control group (WL, *N* = 65). We will test the effect of time (pre-PC vs. post-PC) in interaction with the effect of group (PC vs. WL) on the score obtained in several self-report outcome measures, including scores on burnout symptoms, general wellbeing, and academic achievement as primary outcomes. We hypothesize that PC, compared to WL, should provide evidence of the efficacy of psychological counseling to decrease burnout symptoms and improve general wellbeing and academic achievement.

Moreover, to acquire data on possible mediators or psychological change, we will also assess a large set of secondary outcome variables potentially related to academic burnout, including effort-reward imbalances, basic psychological needs of satisfaction/frustration, intrapersonal and interpersonal emotion regulation, coping strategies and social support. Such variables will be directly and/or indirectly addressed in the psychological counseling sessions (see Section “Intervention” and Table 1). We hypothesize that secondary outcomes variables may be affected by the psychological counseling intervention, mediating or moderating its effects on primary outcomes.

**Table 1 T1:** Summary of psychological counseling intervention features.

**Session**	**Strategy**	**In-session activities**	**Treatment goals**	**TA techniques**
First	Psychoeducation	Information provision on stress, burnout, and coping Information provision about intervention action and goals	Self-awareness	Contract
	Agreement treatment goals	Set goals for time in treatment	Self-awareness	
	Promotion of social support	Introduction of participants and personal experiences sharing	Social support	Therapeutic alliance/group cohesion
Second	Psychoeducation	Information provision on psychological basic needs Identification of basic needs and their satisfaction or frustration in the academic context	Self-awareness	Strokes Therapeutic alliance/group cohesion

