### Participants and sample size

Assuming a medium effect size (Cohen's *d* = 0.50), we estimated with the G^*^Power3 software (Faul et al., 2007) that we need a sample size of 128 participants (i.e., two groups of 64 students) to achieve a power of 0.80 (α = 0.05). Thus, a total of 130 students will be recruited from bachelor's courses at Universitas Mercatorum. Participants are eligible for inclusion according with the following criteria: (a) age > 18 years; (b) clinical levels of academic burnout scores [one standard deviation above the mean MBI-SS total score reported in the validation study by Portoghese et al. (2018)]; (c) attendance of 1^st^ or 2^nd^ year of bachelor course at Universitas Mercatorum; and (d) sufficient knowledge of the Italian language. Additional exclusion criteria aimed at selecting a sufficiently homogeneous group of participants are: (a) previous university degree; (b) other psychiatric diagnoses; (c) other ongoing psychological or psychiatric treatments. Finally, we also excluded (d) attendance of 3^rd^ year of bachelor course, to avoid participants drop-outs due to the course conclusion.

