### Intervention

The online group psychological counseling will be provided to small groups of maximum 10 participants. The intervention will consist of 6 weekly group sessions of 2 h each, based on Transactional Analysis model (Stewart and Joines, 1987; Cannavale and Castagna, 2018). Each session will be conducted by certified psychotherapists trained in Transactional Analysis and an observer co-conductor. In line with treatment goals, intervention strategies will include: (a) psychoeducation about academic-related stress, burnout, and effective strategies to contrast burnout; (b) interventions to promote self-awareness of personal reactions to academic-related stressful events, of the connection between different levels of such reactions (thoughts, emotion, bodily sensations, and behaviors), of psychological satisfaction/frustration needs, and of maladaptive habitual behaviors (e.g., learning style) which may influence academic burnout; (c) intervention to promote initial cognitive restructuring aimed at the identification of more helpful cognitive representations of academic context events (especially cognitive representations of self and others); (d) promotion of social support encouraging social sharing and adaptive social interaction in the group. See Table 1 for an overview of strategies, in-session activities, consistency with treatment goals, and the related TA concepts/techniques.

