### Statistical analysis

Descriptive statistics will be reported for participant recruitment, acceptance, adherence, and dropout rates. Baseline characteristics for each group will be reported to ensure group matching on these variables. To verify the reliability of the eight questionnaires, we will compute test-retest correlations between T1 and T2, and between T1 and T3 (using Pearson's *r* coefficients).

To assess the effects of PC on the outcome variables (MBI-SS, PGWB-S, and academic achievement), mixed model regressions will be utilized, by considering Time (T1, T2, and T3) and Group (PC vs. WL) as fixed factors and subjects as the random factor. This technique will allow us to test the interaction between Time and Group. Our expectation is that PC and WL should differ at T2 and T3, but not at T1, indicating that the PC group should achieve higher scores than the WL group after, but not before, the psychological counseling intervention.

A series of path analyses will be conducted to determine whether the measures obtained from the BPNSFS, ERI-SQ, CERQ-18, DIRE, Brief-Cope, and MSPSS questionnaires mediate the differences in the outcome variables between T1 and T2, and T1 and T3. For each analysis, the exogenous variables will be the outcome measures at T1, the mediators will be the scores in the subscales of the BPNSFS, ERI-SQ, CERQ-18, DIRE, Brief-Cope, and MSPSS questionnaires, and the endogenous variables will be the outcome measures at T1. Since each questionnaire involves multiple subscales, two separate models will be computed for each mediator. For example, for the BPNSFS questionnaire, we will test whether the Autonomy Satisfaction, Competence Satisfaction, Relatedness Satisfaction, Autonomy Frustration, Competence Frustration, and Relatedness Frustration subscales will mediate the associations between the T1 and T2 (or T1 and T3) outcome measures.

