Beside such strengths, the research protocol has also few weaknesses. First, we planned a waiting list design without active control conditions, such as psychological placebo and/or another treatment control groups. We opted for a waiting list design because it is widely used in standard pragmatic trials (Purgato et al., 2015) and it presents relevant ethical advantages (it allows for the provision of care to all research participants). However, due to the lack of an active control condition, our understanding of the mechanisms underlying any possible effect of the intervention will be necessarily partial (Barkauskas et al., 2005; Hart et al., 2008). This could potentially limit the internal validity of the study. Second, according to empirically supported treatments movement (Chambless and Hollon, 1998), experiments must be conducted with treatment manuals. Even if we refer to existing Transactional Analysis manuals to design the psychological intervention, due to the novelty of the field of application a dedicated manual for academic burnout is still missing (but currently in progress). This could lead to inconsistencies in the delivery of the intervention, making it harder to replicate the study and understand which specific aspects of the intervention are most effective. Third, due to the sample size and the group format only an exiguous number of psychotherapists will conduct the interventions. We will control for the effect of the provider in statistical analysis, but our sample size will not allow a complete evaluation of “therapist effects” (Crits-Christoph and Mintz, 1991). The fact that only a small number of psychotherapists will conduct the interventions could introduce therapist effects, where the outcomes are influenced by the specific therapists' skills, styles, or personalities. While the study plans to control for the effect of the provider in statistical analysis, the small sample size may not allow for a complete evaluation of these effects. Finally, while the sample size of 130 participants may be sufficient for detecting large effects, it may not be large enough to detect smaller, yet still meaningful, effects. This could limit the statistical power of the study and the ability to generalize the findings to a larger population. Future studies should overcome such limitations.

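### The primary mixed model has no term for the counseling groups, so its Type I error rises above 5% if outcomes correlate within groups; the promised provider adjustment is not reconciled with it

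*Protocol article*

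**What the plan says.** The Statistical analysis section names the terms of the model for the primary outcomes (MBI-SS, PGWB-S, academic achievement): "by considering Time (T1, T2, and T3) and Group (PC vs. WL) as fixed factors and subjects as the random factor". Group there means PC against WL, not the counseling group a student sits in. The tested effect follows: "This technique will allow us to test the interaction between Time and Group".

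The Intervention section says how PC is delivered: "The online group psychological counseling will be provided to small groups of maximum 10 participants". Table 1 lists group cohesion among the techniques and social support among the goals. The same Intervention section includes encouraging interaction within the group as a strategy. The article describes no counseling groups for WL during the comparison.

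The limitations text at the end of the Statistical analysis section adds: "We will control for the effect of the provider in statistical analysis, but our sample size will not allow a complete evaluation". It gives no term or method for that control. It also says that few therapists will deliver the sessions, that outcomes may depend on who they are, and that no dedicated manual exists yet.

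Participants and sample size gives 128 students (64 per arm) for d = 0.50, power 0.80 and α = 0.05, with 130 to be recruited.

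**The concern.** A random subject effect handles repeated measures on one person. It does nothing for similarity between different people who went through the same sessions together. Here that similarity is plausible by design: cohesion and mutual support are meant to act on the outcome, and the article itself expects differences in delivery between therapists.

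If PC scores at T2 and T3 share a counseling-group component, the PC mean varies more than the model allows. The Group-by-Time test then rejects too often and the confidence intervals are too narrow. The error favours false positives in the main efficacy test. The sample size was also worked out for independent participants, so a correct analysis will have less power than stated.

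**Working it through.** **1. Inputs.** From the article: 65 PC and 65 WL; groups of at most 10; three times; random subject only; d = 0.50, α = 0.05, power 0.80, N = 128. Assumed, because the article does not give them: post-treatment counseling-group ICC of 0.02, 0.05 or 0.10; within-person correlation r of 0.3, 0.5 or 0.7; the group effect absent at T1 and equal at T2 and T3.

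**2. The plan's own figure.** A two-sided two-sample t-test (noncentral t) with d = 0.50 needs 64 per arm, power 0.801. With 65 per arm, power is 0.808. So 128 reproduces, as a calculation for independent participants with no design effect.

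**3. Clusters.** 65/10 = 6.5, so at least 7 groups. Taking two of 10 and five of 9, the size-weighted mean is m = (2×100 + 5×81)/65 = 605/65 = 9.31.

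**4. Type I error of the T2 − T1 contrast.** Set the variance at each time to 1 before the group effect is added, and let v = ICC/(1 − ICC) be the group variance.

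- True variance of the contrast: 4(1 − r)/65 + v·m/65.
- Variance used by the subject-only model: 4·MSE/65, on 256 df, where the residual mean square picks up a little of v: MSE = (1 − r) + v(65 − m)(2/3)/256 = (1 − r) + 0.145v.
- Actual error = 2Φ(−1.96/ratio), where ratio = √(true/model).

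Example, ICC 0.05 and r = 0.5: v = 0.0526. True variance = 0.03077 + 0.00754 = 0.03831. Model variance = 4×0.50763/65 = 0.03124. Ratio = √1.226 = 1.107, and 2Φ(−1.770) = 7.7%.

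| ICC | r = 0.3 | r = 0.5 | r = 0.7 |
|---|---|---|---|
| 0 | 5.0% | 5.0% | 5.0% |
| 0.02 | 5.7% | 6.0% | 6.7% |
| 0.05 | 6.9% | 7.7% | 9.4% |
| 0.10 | 9.0% | 10.6% | 14.0% |

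Simulating the subject-only analysis under the null (20,000 runs per setting) agrees. At r = 0.3 / 0.5 / 0.7 the T2 contrast rejects in 6.0 / 6.3 / 6.4% (ICC 0.02), 6.8 / 7.8 / 9.5% (0.05) and 9.0 / 10.6 / 13.8% (0.10), and in about 5% at ICC 0. The overall 2-df Time-by-Group test gives 5.7 / 5.9 / 6.5%, 6.5 / 7.3 / 9.0% and 8.4 / 10.3 / 13.4%.

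**5. What a correct analysis costs.** This uses a post-treatment comparison of two means, as the plan's sample size does. DE = 1 + (m − 1)·ICC applies to PC only. The variance is V = (DE + 1)/65. The Satterthwaite df is V²/[(DE/65)²/6 + (1/65)²/64], the noncentrality is 0.5/√V, and the interval width relative to the naive one is √((DE + 1)/2) × t(df)/1.979.

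| ICC | DE (PC) | df | t(df) | relative width | power |
|---|---|---|---|---|---|
| 0.02 | 1.17 | 19.4 | 2.090 | 1.041×2.090/1.979 = 1.10 | 0.74 |
| 0.05 | 1.42 | 16.7 | 2.113 | 1.099×2.113/1.979 = 1.17 | 0.69 |
| 0.10 | 1.83 | 14.0 | 2.145 | 1.190×2.145/1.979 = 1.29 | 0.61 |

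**6. Sample size for 80% power.** With equal arms and groups of 10, n per arm = (2 + 9·ICC)(1.96 + 0.84)²/0.25 gives 69, 77 and 92, or 138, 154 and 184 in total. These use the normal approximation and ignore the lost df, so they are on the low side.

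**The case against.** **No ICC is given.** A reader might infer that Type I error exceeds 5% outright and for every primary outcome. The article does not support that. At ICC 0 nothing is inflated, at 0.02 the excess is one or two points at most, and one ICC need not hold for both burnout scores and self-reported exams and grades. A group component already present at T1 and stable over time would cancel in the interaction. This stands, and the point is conditional for that reason.

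**The null needs care.** If groups had no influence on anyone, there would be no shared effect and no inflation. The inflation concerns groups whose effects vary around a zero average, with inference meant for groups and therapists beyond those observed. That is the usual target for a trial of efficacy, but it is an assumption.

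**Provider control is promised.** A reader might infer that the article contradicts itself, or that the promise cannot be kept because WL has no provider. Neither follows. The model sentence does not exclude further terms, a condensed article may leave the form of the adjustment to an analysis plan, and provider coded within PC only can be estimated alongside arm. What remains is that the two statements are not reconciled, and that provider is not the same as counseling group: if one therapist leads several groups, a provider term alone misses the clustering by group.

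**Left to the analysis plan?** The article names the factors of its primary model, and that model does not fit the delivery described. This is a choice already made, not a detail left open. The limitations text concedes only that therapist effects cannot be fully evaluated. It does not say that the standard errors of the primary test are affected.

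**Conclusion.** The point holds in conditional form. Followed as written, the primary model understates the uncertainty of the treatment effect whenever the post-treatment counseling-group ICC is positive. For assumed ICCs of 0.02, 0.05 and 0.10 and within-person correlation of 0.3 to 0.7, the nominal 5% T2 contrast has a true error of about 5–7%, 7–9% and 9–14%. These figures rest on 7 near-equal groups and a group effect that first appears after T1. The design makes a positive ICC plausible, but the article does not establish its size. The stated power of 0.80 holds only for independent participants. Because the flaw sits in the main efficacy test and leans towards false positives, it should be corrected before analysis.

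**What to change.** Replace the model with a partially nested mixed model: fixed Time, Group and their interaction; a random subject effect; and a random counseling-group effect acting in the PC arm only, at T2 and T3. Use Satterthwaite or Kenward-Roger df. Record the counseling-group ID and provider for every PC participant now, since the correct analysis cannot be recovered later without them. State that provider enters within the PC arm only or is reported descriptively, and align the limitations text with that choice.

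The change to the text is small: one more model term and the ID variables. The statistical cost is not: about 14–19 df for the treatment contrast, intervals about 10%, 17% and 29% wider at the three ICCs, and power below 0.80 with 65 per arm. Restate the sample size justification over a stated ICC range, and either raise the target or report the reduced power openly.

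### Read as written, the outcome model assumes one common correlation across unevenly spaced visits and treats students counselled in the same group as independent, although the article promises provider control

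*Protocol article*

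**What the plan says.** The Statistical analysis section of the protocol article specifies mixed model regressions for the MBI-SS, the PGWB-S and academic achievement, with Time (three visits) and Group (PC or WL) "as fixed factors and subjects as the random factor". It adds: "This technique will allow us to test the interaction between Time and Group". The expectation is then put in terms of the two arms differing at T2 and at T3 but not at T1. The section on aims, hypotheses and study design describes the test as time, before versus after counseling, in interaction with group. That is a change-from-baseline contrast.

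The Intervention section gives six weekly sessions in groups of no more than 10. Under Outcomes data collection, T2 follows the last session and T3 comes 3 months after counseling ends.

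The paragraph on weaknesses near the end of the article says: "We will control for the effect of the provider in statistical analysis". It adds that the sample cannot support a complete evaluation of therapist effects. The model sentence contains no provider or counseling-group term.

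**The concern.** Two features of the stated model do not fit the design.

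**Covariance over visits.** A single random intercept per student with independent residuals implies the same variance at T1, T2 and T3 and the same correlation for every pair of visits. The visits are unevenly spaced, so correlations may well differ. Equal variance is also doubtful for the MBI-SS, because students are selected on a high screening score of that same instrument, which can narrow its spread at T1. If the assumed structure is wrong, the model-based standard errors of individual contrasts are wrong too.

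**Clustering in one arm.** Students in the psychological counseling (PC) arm share a group and its conductors, while waiting-list (WL) students do not. If outcomes within a counseling group are positively correlated after the sessions, a model with only a student effect understates the uncertainty of the arm comparison. The article anticipates this by promising provider control, but its model sentence does not deliver it.

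**Working it through.** **1. The plan's own figure.** The Participants and sample size section states "Assuming a medium effect size (Cohen's *d* = 0.50", "we need a sample size of 128 participants (i.e., two groups of 64 students" and "to achieve a power of 0.80 (α = 0.05". For a two-sided two-sample t-test with 64 per arm, the noncentrality is 0.5 × √(64/2) = 2.83 and power is 0.801; with 63 per arm it is 0.795. The figure of 128 is reproduced. It uses no between-visit correlation, so the covariance point below does not alter it. Planned recruitment is 130, or 65 per arm.

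**2. Standard errors of the change contrasts.** The inputs are 65 per arm, complete data, equal variances and no clustering. The correlations r12, r13 and r23 are assumptions, because the article only plans to compute test-retest correlations. Let r̄ be their mean. The random-intercept model uses variance proportional to 2(1 − r̄) for every change, whereas the true value for Tj − T1 is 2(1 − r1j). Hence

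SE ratio (model/true) = √[(1 − r̄)/(1 − r1j)], and type I error = 2[1 − Φ(1.96 × ratio)].

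With r12 = 0.7, r23 = 0.7 and r13 = 0.5, r̄ = 1.9/3 = 0.633:
- T3 − T1: √(0.367/0.5) = 0.856, so the SE is 14% too small and type I error is 9.3%.
- T2 − T1: √(0.367/0.3) = 1.106, so the SE is 11% too large and type I error is 3.0%.

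Other assumed patterns:

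| r12 / r13 / r23 | T2−T1: ratio (type I) | T3−T1: ratio (type I) |
|---|---|---|
| 0.5 / 0.5 / 0.5 | 1.00 (5.0%) | 1.00 (5.0%) |
| 0.6 / 0.5 / 0.6 | 1.04 (4.1%) | 0.93 (6.8%) |
| 0.7 / 0.5 / 0.6 | 1.15 (2.4%) | 0.89 (8.0%) |
| 0.7 per 6 weeks, over 6, 13 and 19 weeks | 1.30 (1.1%) | 0.86 (9.0%) |
| 0.5 / 0.4 / 0.7 | 0.97 (5.8%) | 0.88 (8.4%) |
| 0.4 / 0.4 / 0.7 | 0.91 (7.4%) | 0.91 (7.4%) |
| 0.4 / 0.5 / 0.6 | 0.91 (7.4%) | 1.00 (5.0%) |

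Simulation of 20,000 trials at 0.7/0.5/0.6 gave 2.4% and 8.3%. With equal variances, the T3 − T1 SE is too small only if 2·r13 < r12 + r23, and the T2 − T1 SE is too large only if 2·r12 > r13 + r23.

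**3. PC versus WL at a single visit.** With equal variances and complete data the ratio is 1.00 under every pattern above. If the T1 SD is 0.6 of the later SDs (assumed), the pooled variance is (0.36 + 1 + 1)/3 = 0.787. The ratio at both T2 and T3 is then √0.787 = 0.89, and type I error is 8.2%. Both visits err in the same direction.

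**4. The two-degree-of-freedom interaction test.** For 0.7/0.7/0.5 (T1-T2, T2-T3, T1-T3), the two orthonormal within-student contrasts have variances 1 − 0.5 = 0.5 and (6 − 4×0.7 − 4×0.7 + 2×0.5)/6 = 0.233. Then ε = 0.733²/[2(0.5² + 0.233²)] = 0.88, and the large-sample type I error is 5.5%. At r12/r13/r23 = 0.7/0.5/0.6 it is 5.3%, and at 0.6/0.5/0.6 it is 5.1%.

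**5. Clustering in the PC arm.** Sixty-five students in groups of at most 10 need at least 7 groups, so mean size is m = 65/7 = 9.3. For a post-intervention comparison with equal total variance in each arm and clustering in PC only, true variance/model variance = 1 + (m − 1) × ICC/2. The ICC is an assumption.

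| ICC | Variance ratio | 1.96/√ratio | Type I error |
|---|---|---|---|
| 0.01 | 1.041 | 1.921 | 5.5% |
| 0.05 | 1.207 | 1.784 | 7.4% |
| 0.10 | 1.414 | 1.648 | 9.9% |

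**The case against.** A reader might infer that the follow-up contrast certainly rejects too often and the post-intervention contrast too rarely. The documents do not support that. They give no correlations, and counseling between T1 and T2 could lower r12 relative to r23. In that case the T2 − T1 standard error can also be too small, and in one pattern above the T3 − T1 standard error is exact.

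A reader might also take 9.3% as the error rate of the planned test. It is not. The joint interaction test is at about 5.5% under the same correlations, and the comparisons at T2 and T3 that the article describes do not depend on the correlation pattern when variances are equal and data complete. Both limits stand. Even so, the article does name a pre/post-by-group contrast, which is sensitive to the pattern, and unequal variances would affect the single-visit comparisons.

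It is also fair to say that the sentence does not exclude a residual covariance structure or robust standard errors, that a condensed article may leave these to a fuller document, and that the provider promise shows the sentence is not the whole model. So the article cannot be said to have ruled out a sound analysis. But the point concerns the structure that the sentence does name, with students as the only random factor, and its mismatch with the provider statement in the same article. That mismatch needs no assumed correlation.

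**Conclusion.** The point holds in a conditional form. As worded, the model imposes equal variances and one correlation on unevenly spaced visits and omits the clustering that the article itself raises.

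If correlation falls with elapsed time, as in the 0.7/0.7/0.5 illustration, type I error is about 9% for the T3 − T1 contrast and about 3% for T2 − T1. The direction is not established by the documents, and the joint interaction test is little affected. Those figures assume complete data, equal variances, equal arms and no clustering.

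The clustering effect is separate: about 5.5% to 9.9% over assumed ICCs of 0.01 to 0.10, with seven PC groups averaging 9.3 students. Neither part shows the sample size calculation to be misreported, since 128 reproduces. The change is worth making because it remains valid whichever correlation pattern occurs.

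**What to change.** In the Statistical analysis section, replace the random intercept alone with an unstructured covariance over T1, T2 and T3, with Kenward-Roger degrees of freedom. In large samples this brings the model/true SE ratio to 1.00 for every contrast. Add a random counseling-group (or provider) effect in the PC arm only, so that the model matches the statement on provider control in the paragraph on weaknesses.

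The cost is one or two sentences, a few extra variance parameters (six instead of two for the three visits, plus the group or provider component) and slightly wider intervals. With 130 students the visit covariance is readily estimated. With possibly only seven counseling groups the cluster variance will be imprecise, in keeping with the article's own caveat about therapist effects.

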### Outcomes data collection

Outcome variables will be assessed at T1, T2, and T3, using a Google Form. At each time, participants of the two groups will be required to fill in the eight self-report questionnaires described above (MBI-SS, PGWB-S, BPNSFS, ERI-SQ, CERQ-18, DIRE, Brief-Cope, and MSPSS). Baseline data (T1) will be collected after brief assessment interview (once informed written consent has been obtained by the participant). T2 data will be collected after the end of the last PC session. Finally, 3 months after the end of PC, participants will be contacted electronically via email and invited to fill in the Google Form to obtain T3 data.

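### The mediation path models name neither Group nor the mediators' own T1 scores, so stable differences between students can be reported as mediation, and adding Group alone would not prevent this

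*Protocol article*

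**What the plan says.** Three parts of the protocol article bear on this.

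- **Purpose** (Aims, hypotheses, and study design). The authors expect that "secondary outcomes variables may be affected by the psychological counseling intervention, mediating or moderating its effects on primary outcomes". This is a hypothesis about how the intervention works.
- **Model** (Statistical analysis). The section reads: "For each analysis, the exogenous variables will be the outcome measures at T1, the mediators will be the scores in the subscales". Six questionnaires supply these subscales: MSPSS, Brief-Cope, DIRE, CERQ-18, ERI-SQ and BPNSFS. The sentence ends by saying that "the endogenous variables will be the outcome measures at T1". The worked example in the same paragraph has the subscales tested for whether they "will mediate the associations between the T1 and T2 (or T1 and T3) outcome measures", so the later outcome is evidently T2 or T3. The T1 outcome is therefore the predictor whose link to the later outcome is to be mediated. Group is not mentioned, no time point is given for the mediators, and no change score is described.
- **Data** (Outcomes data collection). "At each time, participants of the two groups will be required to fill in the eight self-report questionnaires described above". All six mediator questionnaires are among the eight, so every mediator has a T1 score in both arms.

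**The concern.** A subscale score after counseling is the sum of the student's usual level and whatever changed. The protocol itself describes the CERQ-18 as a measure of habitual strategies, and it plans T1-T2 and T1-T3 correlations as evidence of questionnaire reliability, which presumes largely stable scores. If students who habitually cope better, or feel better supported, also tend to have less burnout at every visit, the later mediator will predict the later outcome even when changing the mediator does nothing. The T1 outcome absorbs only part of this, because a single noisy score measures a stable level imperfectly.

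Two omissions are involved. Without Group, the models cannot address the stated hypothesis. Without the mediator's T1 score, the mediator-outcome path is confounded by stable differences between students. Repairing only the first leaves the second: randomisation balances the arms and so protects the Group-mediator path, but students are not randomised to mediator levels. At stake is whether the trial names mechanisms that it has not shown.

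**Working it through.** **Plan's own figure.** The only computed figure in the document is the sample size: "we need a sample size of 128 participants (i.e., two groups of 64 students) to achieve a power of 0.80 (α = 0.05"). For d = 0.50, an exact two-sided t-test needs 64 per arm (power 0.801); the planned 65 per arm give 0.808. The figure reproduces, and the point does not depend on it. It supplies N = 130 and the 0.5 SD effect used below.

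**Assumptions (not in the documents).** Each score is a stable trait plus independent visit noise, with variance 1. The share of variance that is stable is s = 0.6 to 0.8. The mediator and outcome traits correlate at r = 0.3 to 0.7. The mediator has no effect on the outcome. There is one mediator per model, measured at T2. Mediation is declared when both paths are significant at 0.05.

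**Hand check at r = 0.5, s = 0.7.** Two scores of the same measure correlate at s = 0.70; a mediator score and an outcome score correlate at k = r·s = 0.35.

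1. Mediator-outcome path, adjusting for the T1 outcome only: b = (k − s·k)/(1 − k²) = (0.35 − 0.245)/0.8775 = 0.120. The true value is 0.
2. Adding the T1 mediator: the T1 and T2 mediators relate to the outcome scores identically, so they share one coefficient b. With c the coefficient of the T1 outcome, c + 0.70b = 0.70 and 0.35c + 1.70b = 0.35. Hence 1.455b = 0.105 and b = 0.072. The bias shrinks by about 40% but does not vanish.
3. Chance of false mediation with Group in the model and a 0.5 SD shift in the mediator:
   - Without the T1 mediator: SE(b) = √(0.497/(126 × 0.8775)) = 0.067, ratio 1.78, significant in about 42% of trials. Group-mediator path: 0.5/√(4/130 × 0.8775) = 3.04, significant in about 86%. Product about 36%.
   - With it: SE(b) = √(0.495/(125 × 0.497)) = 0.089, ratio 0.81, about 12%. Group-mediator path: 0.5/√(4/130 × 0.497) = 4.04, about 98%. Product about 12%.

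**Simulation** (N = 130, 2000 trials per setting, s = 0.6, 0.7 and 0.8; ranges are over s). At r = 0.5, s = 0.7 it gives 36.1% and 12.3% for step 3, matching the hand check.

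| Model | Group effect | r = 0.3 | r = 0.5 | r = 0.7 |
|---|---|---|---|---|
| As written, T2 mediator | none | 10-12% | 38-42% | 74-77% |
| As written + T1 mediator | none | 1-2% | 4-7% | 14-26% |
| As written + T1 mediator | 0.5 SD on both | 6-7% | 18-21% | 49-54% |
| Group as exposure, T1 outcome | 0.5 SD on both | 13-15% | 31-37% | 66-72% |
| Group as exposure, T1 outcome and T1 mediator | 0.5 SD on both | 6-7% | 9-15% | 19-32% |

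A separate simulation in which counseling shifts only the mediator gave 12-68% without the T1 mediator and 6-31% with it, Group being in both models. With Group as the exposure and no group effect at all, false mediation stays below 4% either way. In that model the problem therefore arises for mediators that counseling does move.

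**Mediator timing.** If T1 subscale scores were meant as the mediators, the model as written with no group effect gives 10-78%. If change scores were meant, it gives under 1%.

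**The case against.** The case against has several parts.

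*The article may condense a fuller covariate list, and the sentence contains an evident slip.* A reader might infer that the T1 mediator scores are certainly left out of every analysis. The text does not go that far: mediator timing is unstated, change scores are not excluded, and the analysis plan is not shown. But the sentence does state the exogenous variables for each analysis, and that statement is what needs correcting.

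*The larger defect is the missing Group.* This stands. A reader might take the 12-70% range as the error rate of the planned analysis, or regard the T1 outcome as an adjustment covariate. Neither is supported: that range belongs to a model with Group, which the plan does not contain, and the T1 outcome is the predictor being mediated, although its direct path does adjust the later outcome for baseline. Likewise, the better precision of the Group-mediator path would be gained only after Group is added. Nor would adding only the T1 mediator suffice; with 0.5 SD group effects it still leaves 6-54%.

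*The size rests on one mediator per model.* This stands in part. The BPNSFS example may mean that six subscales are fitted together. With Group included, and subscale traits assumed to correlate at 0.5, false mediation per subscale without the T1 scores was 5-35% for six subscales and 5-25% for nine. At r = 0.3 the T1 scores made almost no difference (about 5% either way). The chance of at least one false result among six was 26-95% without them and 25-52% with them.

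*The article already concedes that understanding of mechanisms will be partial.* It does, but because there is no active control, which is a different and less easily remedied reason.

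**Conclusion.** The point holds in this form: the path models as specified name neither Group nor the mediators' T1 scores, and stable differences between students can therefore be reported as mediation. Under the stated assumptions, false mediation is roughly 10-75% for the model as written with no group effect, and roughly 12-70% once Group is added and counseling moves the mediator by 0.5 SD. Including the T1 mediator as well brings the latter to roughly 6-33%. The direction is secure; the rates depend on correlations that the documents do not give, and the gain may be smaller when several subscales are modelled jointly.

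A reader might infer that the efficacy result is compromised or that the repaired model would be free of bias. Neither follows. The Time by Group mixed model is separate and unaffected, and one noisy baseline score removes only part of the confounding. This is a correction to a secondary analysis that should be made before any mechanism is reported.

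**What to change.** In every path model:

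1. Make Group the exogenous exposure.
2. State that the mediator is the T2 (or T3) subscale score and that the endogenous variable is the T2 (or T3) outcome, correcting the printed T1.
3. Include the T1 score of the same subscale and the T1 outcome as covariates in both the mediator equation and the outcome equation.
4. Say whether the subscales of a questionnaire are fitted singly or jointly.
5. State that residual mediator-outcome confounding remains possible and that the results are exploratory.

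The cost is a few sentences in the Statistical analysis section and no new data. Beyond Group and the T1 outcome, each equation gains one covariate per mediator. If the CERQ-18 subscales are modelled jointly, that is up to nine per equation, and the outcome equation would then hold nine correlated T1 and later pairs with at most 130 students. This is a reason to settle item 4 in advance.
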